### Randomization and Blindness

During the recruitment period, participants will be allocated 1:1 to two groups (*n* = 30) by computer-generated randomization procedures using opaque envelopes. A research assistant not involved in the study will prepare the envelopes before the study. After recording baselines measures, participants will be randomly allocated to either the intervention or the control group by the treating physicians who will open the sealed opaque envelopes. In order to minimize selection bias, patients and assessors involved in the trial will be masked to treatment allocation. All outcome measurements will be assessed by two observers blinded to the treatment plan, any disagreement will be resolved by reaching a consensus between the two. If no consensus can be reached, a third observer blinded to the treatment assignment and not involved in the clinical treatment plan will have a final decision. Finally, an independent investigator blinded to the treatment assignment will collect the data of outcomes and information of the group, and analyze them.

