### Estimation of Sample Size

There is no data available for reference because no completed clinical study of C+P in AIS patients without EVT currently exists. However, Hertzog has suggested that 10 to 20 patients in each group are sufficient to assess the feasibility of a pilot study (22) while Dobkin has shown that 15 patients in each group is usually enough to decide whether a larger multicenter trial should be conducted (23). Therefore, our goal is to recruit 15 patients in each group, a similar number of samples was selected for another protocol (24). The results of this study should be able to determine the initial safety and feasibility of intravenous infusion of C+P in AIS patients. The data will be used to estimate sample size and conduct a power calculation to plan a phase-2 trial for efficacy.

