### Statistical Analyses

The endpoint event analysis is based on the intention-to-treat (ITT) principle, including all randomly enrolled subjects. If compared to the control group, the treatment group did not have an increase in the incidence of adverse reactions and there was no difference in 90 days prognosis between the two groups, we would move forward with a phase-2 trial.

Categorical variables including the proportion of good functional outcomes and the frequency of adverse events will be presented as counts and percentages. χ^2^-test, Fisher exact-test, or continuity correction will be used where appropriate for comparison between the two groups. If the continuous variables including NIHSS score and infarct volume conform to the normal distribution, it shall be indicated by mean ± standard, and tested by *t*-test, and if it does not conform to the normal distribution, it shall be indicated by median and interquartile range and tested by Mann-Whitney *U*-test. *p* < 0.05 will be considered statistically significant. SPSS 22.0 software will be used for statistical analysis.

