The RICHES study is designed to identify the safety, feasibility, and secondarily any possible efficacy of intravenous administration of C+P in AIS patients. The preliminary results will provide clues for the design of future clinical trials. If there is no significant difference in the incidence of drug-related adverse events between the experimental group and the control group, further clinical trials will be indicated. Based on past basic research and previous clinical studies, we predict that chlorpromazine and promethazine is safe for patients with acute ischemic stroke. The current study may suggest a neuroprotective role in AIS, and warrant a randomized controlled trial (RCT).

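### The go condition for phase 2 asks for no difference in 90-day prognosis without a direction, so a significant benefit fails it while moderate harm usually meets it

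*Protocol article*

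**What the plan says.** Three places in the protocol article bear on what follows this pilot.

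- **Statistical Analyses.** Two conditions are set relative to control: "the treatment group did not have an increase in the incidence of adverse reactions and there was no difference in 90 days prognosis". The second leads straight to the decision: "there was no difference in 90 days prognosis between the two groups, we would move forward with a phase-2 trial". The first condition is directional (no increase) and the second is not. Neither has a margin. The same section fixes the significance criterion: p below "0.05 will be considered statistically significant".
- **Discussion, closing paragraph.** Here the condition is "no significant difference in the incidence of drug-related adverse events between the experimental group and the control group, further clinical trials will be indicated". Prognosis is not mentioned, and the events are limited to drug-related ones. The same paragraph goes on to say that the study may suggest neuroprotection and so justify a randomised trial.
- **Estimation of Sample Size.** The target is 15 per group, and "The data will be used to estimate sample size and conduct a power calculation to plan a phase-2 trial for efficacy".

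Functional independence (mRS 0-2), NIHSS and infarct volume are listed as efficacy outcomes, and preliminary efficacy is a stated aim.

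**The concern.** The go decision is the main product of a pilot. For a candidate neuroprotectant, the prognosis condition should guard against a worse outcome. As worded it treats better and worse alike: any declared difference, including one in favour of C+P, leaves the condition unmet. In the other direction, if a non-significant test counts as no difference, 15 patients per arm give little chance of noticing a clinically serious loss. The condition is thus least useful where it matters, and a favourable result has no place under it. The Discussion adds a second version of the rule, so a reader cannot tell which one the sponsor will apply.

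**Working it through.** **Inputs.** From the document: 15 per arm ("our goal is to recruit 15 patients in each group"), 1:1 allocation, significance at 0.05, and chi-square, Fisher or continuity-corrected tests for proportions. Assumed, because the document does not give them: a two-sided test, a control rate of mRS 0-2 of 50%, the true rates on C+P shown below, and that no difference means p ≥ 0.05. The Discussion's reference to a significant difference supports that last assumption.

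**The plan's own figure.** The sample size rests on pilot-study rules of thumb. 2 × 15 = 30 agrees with the stated n = 30. There is no effect size or power to reproduce.

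**Method.** Let X be the number with mRS 0-2 on control, Bin(15, pc), and Y the number on C+P, Bin(15, pt). P(condition met) = Σ P(X=x)·P(Y=y) over all 16 × 16 tables with two-sided p ≥ 0.05.

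| True mRS 0-2, control v C+P | Condition met, Fisher | Condition met, uncorrected chi-square |
|---|---|---|
| 50% v 30% | 90% | about 80% |
| 50% v 25% | 84% | 71% |
| 50% v 20% | 75% | 58% |
| 50% v 10% | 46% | 27% |
| 50% v 70% | 90% | about 80% |
| 50% v 80% | 75% | 58% |

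For 50% v 25%, P(significant) is 0.157 by Fisher and 0.293 by chi-square; 1 − 0.157 = 0.843 and 1 − 0.293 = 0.707. For 50% v 70%, P(significant in favour of C+P) is 0.096 and 0.194; these trials fail the condition because C+P did better.

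**Single results.** 8/15 on control against 3/15 on C+P is a deficit of 5/15 = 33 points. Fisher gives p = 0.128 and chi-square p = 0.058, so it counts as no difference by either test. 6/15 against 13/15 in favour of C+P gives Fisher p = 0.021, so the condition is not met.

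**Both conditions together.** As an illustration, take hypotension at 10% v 30%, mRS 0-2 at 50% v 30%, independence, and Fisher for both. The pass probability is (1 − 0.149) × (1 − 0.096) = 0.77, against 0.90 for prognosis alone.

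**If no difference is read numerically.** Equal mRS 0-2 counts occur in only about 14% of trials when both true rates are 50%, so the condition could hardly be met.

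**Precision.** The 95% half-width is 1.96·√[pc(1−pc)/15 + pt(1−pt)/15]. At 40% v 20% it is 32 points; at 50% v 50% it is 1.96·√(0.50/15) = 36 points.

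**Replacement rules, at an illustrative margin of 20 points (3/15).** The range in the second column depends on whether a deficit of exactly 3/15 passes.

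| True rates | Pass, point estimate | Pass, 95% lower limit must exclude a 20-point loss |
|---|---|---|
| 50% v 50% | 82-90% | 18% |
| 50% v 70% | 98-99% | 60% |
| 50% v 25% | 31-46% | 1% |

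The interval rule would turn away most drugs with equal outcomes and 40% of trials of a drug with a 20-point benefit. At this sample size only the point-estimate rule is workable.

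**The case against.** A reader might infer that a benefit would stop development. The text does not support that. Statistical Analyses gives a condition under which the sponsor would proceed and no decision for any other result, and the Discussion's last lines treat a neuroprotective signal as a reason for a further trial. The authors probably meant not worse. What stands is that the only rule in the Methods does not say so, and a favourable result falls outside it.

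A reader might also infer that the two sections contradict each other. Both give sufficient conditions, one for a phase-2 trial and the other a closing remark that "further clinical trials will be indicated". The second is less complete, which calls for alignment, but it is not a logical contradiction.

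A third inference is that phase 2 will be sized on the observed difference. Estimation of Sample Size does not say which data will be used. Control rates, standard deviations and retention are legitimate inputs from a pilot.

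On size, it is fair to object that 84% is the Fisher figure for one condition of two. The chi-square test gives 71%, and the adverse-reaction condition, with safety outcomes that include death and neurological deterioration, would catch some harmful trials. Very large harm (50% v 10%) fails the prognosis condition about half the time or more. None of this alters the finding that moderate harm usually meets the prognosis condition.

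Finally, low power is normal in a pilot, the article itself warns of spurious results from a small sample, and an independent physician watches safety during the trial. These points limit the severity. They do not make non-significance evidence of no harm.

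**Conclusion.** The point holds in a limited form. The prognosis condition is wrongly stated: it has no direction, so a significantly better outcome does not meet it, while a true fall in mRS 0-2 from 50% to 25% meets it in 71-84% of trials. A true rise to 70% fails it in roughly 10-20%, depending on the test. These figures concern this condition alone and rest on the assumed 50% control rate, a two-sided 0.05 level, and reading no difference as non-significance. The Discussion's version omits prognosis and needs aligning. The wording governs a later decision and does not affect randomisation, participants' safety during the trial or the validity of its estimates. It should be fixed, but it is not a critical fault.

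**What to change.** In Statistical Analyses, make the prognosis condition one-directional: it fails only if the observed 90-day mRS 0-2 rate on C+P is lower than control by more than a margin that the sponsor names in advance. Judge it on the point estimate. Report the 95% confidence interval for information (half-width about 32-36 points) and do not require it to exclude the margin. State that a better outcome never blocks progression, and say whether a deficit equal to the margin passes. Put the same rule, with the same class of adverse events, in the closing Discussion.

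As an optional clarification, Estimation of Sample Size could say that the observed treatment difference will not be the target effect for phase 2. Its present wording is not an error.

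The cost is a few sentences and no extra data, but the sponsor has to choose and defend a margin. A drug with equal outcomes will sometimes fail by chance: about 10-18% of the time at the illustrative 20-point margin with both rates at 50%. Some harm will still pass: 31-46% of trials at 50% v 25%, against 71-84% under the present wording.

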## Abstract

**Background:** Following an acute ischemic stroke (AIS), rapidly initiated reperfusion therapies [i. e., intravenous thrombolysis (IVT) and endovascular treatment (EVT)] demonstrate robust clinical efficacy. However, only a subset of these patients can benefit from these therapies due to their short treatment windows and potential complications. In addition, many patients despite successful reperfusion still have unfavorable outcomes. Thus, neuroprotection strategies are urgently needed for AIS patients. Chlorpromazine and promethazine (C+P) have been employed in clinical practice for antipsychotic and sedative purposes. A clinical study has also shown a neuroprotective effect of C+P on patients with cerebral hemorrhage and subarachnoid hemorrhage. The safety, feasibility, and preliminary efficacy of intravenous administration of C+P in AIS patients within 24 h of onset will be elucidated.

**Methods:** A prospective randomized controlled trial is proposed with AIS patients. Participants will be randomly allocated to an intervention group and a control group with a 1:1 ratio (*n* = 30) and will be treated with standard therapies according to the current stroke guidelines. Participants allocated to the intervention group will receive intravenous administration of C+P (chlorpromazine 50 mg and promethazine 50 mg) within 24 h of symptom onset. The primary outcome is safety (mainly hypotension), while the secondary outcomes include changes in functional outcome and infarction volume.

**Discussions:** This study on Rapid Intervention of Chlorpromazine and Promethazine for Hibernation-like Effect in Stroke (RICHES) will be the first prospective randomized controlled trial to ascertain the safety, feasibility, and preliminary efficacy of intravenous C+P as a neuroprotection strategy in AIS patients. These results will provide parameters for future studies, provide insights into treatment effects, and neuroprotection with phenothiazine in AIS.

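### The stated analysis is testing-only, with no between-arm estimate or confidence interval named for any outcome, which does not suit a 15-per-arm pilot meant to judge initial safety and inform phase 2

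*Protocol article*

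**What the plan says.** All from the protocol article.

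- **Statistical Analyses, categorical outcomes.** "Categorical variables including the proportion of good functional outcomes and the frequency of adverse events will be presented as counts and percentages". The comparison is a test: chi-square, "Fisher exact-test, or continuity correction will be used where appropriate for comparison between the two groups".
- **Statistical Analyses, continuous outcomes (NIHSS, infarct volume).** If normal, "it shall be indicated by mean ± standard, and tested by" a *t*-test. If not, "it shall be indicated by median and interquartile range and tested by" a Mann-Whitney *U*-test. A p-value below 0.05 "will be considered statistically significant".
- **Primary Outcomes.** The main safety parameter is the incidence of hypotension needing intervention, a proportion in each arm.
- **Estimation of Sample Size.** "our goal is to recruit 15 patients in each group", taken from published rules of thumb for pilot studies. The section adds: "The results of this study should be able to determine the initial safety and feasibility of intravenous infusion of C+P in AIS patients". The data are also to feed the sample-size and power calculation of a phase-2 trial.
- **Abstract.** "These results will provide parameters for future studies, provide insights into treatment effects".
- **Decision to proceed.** Statistical Analyses would move to phase 2 if adverse reactions are not increased and 90-day prognosis does not differ. The end of the Discussion ties further trials to the absence of a significant difference in drug-related adverse events.

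No section names a risk difference, mean or median difference, or confidence interval.

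**The concern.** The stated aims are matters of estimation: how often hypotension occurs on C+P, how far the arms differ, and how variable the outcomes are. The stated method is a set of tests. At 15 per arm, a p-value above 0.05 says little about how large a harm or benefit remains possible, and the article treats the absence of a difference as a reason to continue.

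Followed as written, a sizeable excess of hypotension on C+P could be tabulated with a non-significant p-value and nothing beside it to show what the data still allow. An event-free C+P arm could be read as reassuring without its upper limit. Phase-2 planners would have to work out the effect and its uncertainty themselves, and for skewed outcomes the planned summaries would not directly let them.

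**Working it through.** **1. The plan's own figure.** The target is 15 per group, 2 × 15 = 30 in total. It matches the rules of thumb the article cites (10 to 20 per group, and 15 per group). No power, effect size, event rate, SD or precision target is given, so there is no formula to reproduce. Below, n = 15 per arm and tests are two-sided (the article does not state sidedness). Event counts, true rates and SDs are illustrative assumptions.

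**2. What p < 0.05 requires for hypotension.** With x events on C+P and none on control, the two-sided Fisher p is 2 × C(15,x) / C(30,x):

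- x = 3: 2 × 455 / 4,060 = 0.22
- x = 4: 2 × 1,365 / 27,405 = 0.10
- x = 5: 2 × 3,003 / 142,506 = 0.042

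So at least 5/15 (33%) is needed against 0/15. Against 1/15, 6/15 gives p = 0.08 and 7/15 gives p = 0.035.

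Exact Fisher power at assumed true rates (C+P v control): 8% for 20% v 5%, 27.5% for 30% v 5%, 52% for 40% v 5%.

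**3. What an interval would add.** Risk difference with Newcombe 95% interval, in percentage points:

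| Outcome, C+P v control | Fisher p | Difference | 95% interval |
|---|---|---|---|
| Hypotension 0/15 v 0/15 | 1.00 | 0 | -20 to +20 |
| Hypotension 3/15 v 0/15 | 0.22 | +20 | -4 to +45 |
| Hypotension 4/15 v 0/15 | 0.10 | +27 | +1 to +52 |
| Hypotension 3/15 v 1/15 | 0.60 | +13 | -13 to +39 |
| mRS 0-2 in 9/15 v 6/15 | 0.47 | +20 | -14 to +49 |

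In the 4/15 row, the interval just excludes zero while Fisher's test does not reach 0.05. The two methods are not inversions of each other, so this row should not be over-read. It does show that the interval method must be chosen in advance.

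**4. An event-free C+P arm.** Exact upper limit for 0/15:

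- Two-sided 95%: 1 - 0.025^(1/15) = 21.8%
- One-sided 95%: 1 - 0.05^(1/15) = 18.1%

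If the true rate were 5%, no event would be seen in 15 patients with probability 0.95^15 = 46%.

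**5. Continuous outcomes.** The 95% half-width of a mean difference is t(0.975, 28) × SD × √(2/15) = 0.748 × SD. For an assumed NIHSS SD of 4, 6 or 8 this is 3.0, 4.5 or 6.0 points. The article's own definition of neurologic deterioration is a rise of 4 points. A pooled SD from 30 patients has a 95% interval of 0.79 to 1.35 times its estimate.

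**6. What can be recovered from the planned summaries.** Counts with n give the risk difference and its interval. Means with SDs and n give the mean difference and its interval. A median with interquartile range directly gives neither an SD for a sample-size formula nor an interval for a location shift.

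**The case against.** The strongest reply is that this is an absence in a short journal article. The section lists summaries and tests without saying that nothing else will be reported, and effect measures and interval methods are commonly left to an analysis plan that is not shown. This stands in part: a reader might infer that the article rules out estimates and intervals, and it does not. The point survives because the article commits to a method, tests at 0.05, alongside aims of estimation and a decision to proceed on no difference. That mismatch can be judged from the article alone.

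A reader might also infer that the pilot cannot supply the promised parameters. That goes too far. Arm proportions and means with a spread measure are ordinary sample-size inputs, and step 6 shows that most differences and intervals can be derived from them. Only the median and interquartile-range branch leaves a real gap.

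Nor does the article claim to prove safety. It speaks of initial safety, lists the small single-center sample as a limitation, and calls the results preliminary. It also cannot be said that nearly every p-value will exceed 0.05, since that depends on unknown effects.

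Finally, much of the harm comes from reading non-significance as grounds to proceed, and intervals would not make 15 per arm more precise. Both are true. But rewording the decision rule alone would not change what is reported for hypotension, other safety events, mRS, NIHSS or infarct volume.

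**Conclusion.** The concern holds in limited form. The stated analysis is testing-only, and the effect and its precision are not planned results for any outcome, the primary one included. At 15 per arm this matters: a hypotension excess of 20 to 27 points (3/15 or 4/15 v 0/15) would be reported as non-significant, and an event-free C+P arm excludes only rates above about 22% (two-sided) or 18% (one-sided).

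The limits for 0/15 and the 5/15 threshold follow from n = 15 and a two-sided 0.05 test. The other counts, rates and SDs are illustrations. Fewer evaluable patients would widen every interval. The change is worth making before analysis, but it does not call the sample size or the trial's conduct into question.

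**What to change.** **Statistical Analyses.** Make the between-arm difference with a 95% confidence interval the reported result of each comparison, with the p-value secondary:

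- hypotension, each other safety event and mRS 0-2: risk difference with a Newcombe or exact interval, one method named in advance;
- NIHSS and infarct volume: mean difference, or Hodges-Lehmann shift where the data are not normal, with its interval, and SDs reported in either case;
- C+P event rates: an exact interval for each.

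**Estimation of Sample Size.** Qualify the statement about determining initial safety with the precision delivered: if no hypotension is seen in 15 C+P patients, only rates above about 22% (two-sided 95%) or 18% (one-sided 95%) are excluded.

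**Cost.** Wording only; no extra patients, visits or data. The published intervals will be wide and the safety claim will read less favourably.

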
## Methods

### Study Design

This is a single-center, prospective randomized controlled trial. It will be performed in patients with acute ischemic stroke (AIS) onset within 24 h. Participants meeting inclusion criteria but not exclusion criteria will be randomly allocated to the C+P or the control group whether they received IVT or not. Participants allocated to the intervention group will receive intravenous administration of C+P within 24 h of symptom onset, within the first 60 min of administration. C+P will be administered after rt-PA if the patients received IVT. Seeing that early mechanical thrombectomy has an absolute difference in the rate of functional independence, as compared with alteplase alone (19, 20), this study will not include patients treated with EVT. *Via* the medical records, the demographic information, chronic medical history (diabetes, hypertension, hyperlipidemia, coronary heart disease), smoking history, alcohol drinking history, and NIHSS score at admission will be collected. Magnetic resonance imaging (MRI) will be performed at baseline and on days 3 and 90. NIHSS and mRS will be evaluated at baseline and immediately after administration, and on days 2, 3, 7, 14, and 90. All participants or proxies will be informed of potential risks and possible benefits and consented for this study. The consent will be provided to a legal representative if the patients do not have the capacity to consent. This study was approved by the ethics committee of Luhe Hospital, Capital Medical University, Beijing, China and has been registered at www.chictr.org.cn with ChiCTR2000038727. An independent physician will monitor the health and safety of the participants.

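### NIHSS and infarct volume are compared without using their baseline values; the tests are valid on average, but a fixed baseline-adjusted analysis would be more precise at almost no cost

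*Protocol article*

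**What the plan says.** All references are to the protocol article.

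- **Test.** Under Statistical Analyses the rule begins "If the continuous variables including NIHSS score and infarct volume conform to the normal distribution", in which case means and a t-test are used. Otherwise, "if it does not conform to the normal distribution, it shall be indicated by median and interquartile range and tested by Mann-Whitney" U-test. The threshold is p below 0.05; sidedness is not given. No model, covariate or change from baseline is named.
- **Baseline data.** Study Design states: "NIHSS and mRS will be evaluated at baseline and immediately after administration, and on days 2, 3, 7, 14, and 90". It also states: "Magnetic resonance imaging (MRI) will be performed at baseline and on days 3 and 90". Both outcomes therefore have a baseline measurement.
- **Severity at entry.** The inclusion criteria limit NIHSS to 6 to 25.
- **Allocation.** Under Randomization and Blindness, "participants will be allocated 1:1 to two groups", using sealed envelopes. No stratification is stated.
- **Size and purpose.** Under Estimation of Sample Size, "our goal is to recruit 15 patients in each group". The same section says the data will serve the sample size and power calculation for a phase-2 efficacy trial.

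**The concern.** Stroke severity and lesion size at entry would be expected to predict the same measures at follow-up. A two-sample test of the follow-up values leaves that predictable part in the error term. It also carries any chance difference between the arms at entry into the estimated effect, in proportion to the correlation. With 15 per arm, a wide entry range and no stated stratification, nothing in the described design or analysis limits this.

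The normality check adds a smaller problem: the data decide whether the result is a difference in means or a rank comparison. If the rank branch is taken, the stated summary is medians and interquartile ranges, which are less convenient for phase-2 planning than an adjusted difference with its residual SD.

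At stake is the quality of the preliminary efficacy estimates. The primary outcome, hypotension, is not affected.

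**Working it through.** **The plan's own figure.** The 15 per group comes from pilot-study rules of thumb. No effect size, SD or power is given, so no formula can reproduce it. It is taken as stated.

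**Inputs.** From the document: n = 15 per arm, 1:1 allocation, alpha 0.05 (two-sided assumed). Assumed, because the document gives neither: a baseline-to-outcome correlation ρ of 0.3 to 0.8, and a baseline NIHSS SD of 5 (range 4 to 6). SD units below assume equal spread at baseline and follow-up.

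**1. Precision.** In SD units the unadjusted standard error is √(2/15) = 0.365. With ANCOVA on the baseline value it is √(1 − ρ²) × √(2/15). The equivalent unadjusted sample is 15/(1 − ρ²).

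| ρ | Variance left, 1 − ρ² | SE, adjusted | Equivalent n per arm | Variance of change score, 2(1 − ρ) |
|---|---|---|---|---|
| 0.3 | 0.91 | 0.348 | 16.5 | 1.40 |
| 0.5 | 0.75 | 0.316 | 20.0 | 1.00 |
| 0.7 | 0.51 | 0.261 | 29.4 | 0.60 |
| 0.8 | 0.36 | 0.219 | 41.7 | 0.40 |

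Estimating the slope in 30 patients inflates the adjusted variance by about 1 + 1/26 = 27/26. The second column then becomes 0.945, 0.779, 0.530 and 0.374, or about 15.9, 19.3, 28.3 and 40.1 per arm. The gain vanishes when 1 − ρ² = 26/27, that is at ρ = √(1/27) ≈ 0.19.

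The last column is relative to 1 for the unadjusted comparison. A change score is worse than no adjustment below ρ = 0.5, equal at 0.5, and worse than ANCOVA throughout this range.

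**2. Chance imbalance in NIHSS.** The SE of the baseline difference is 5 × √(2/15) = 1.83 points. The chance of a difference of 2 or more points in either direction is 2 × [1 − Φ(2/1.83)] = 27%. With SD 4 (SE 1.46) it is 17%; with SD 6 (SE 2.19) it is 36%.

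**3. Effect on the estimate.** In SD units, a baseline difference above 0.5 SD occurs in 2 × [1 − Φ(0.5/0.365)] = 17% of trials. A 0.5 SD imbalance shifts the unadjusted follow-up difference by 0.5ρ: 0.15 SD at ρ = 0.3, up to 0.40 SD at ρ = 0.8. Given that imbalance, the false-positive rate is about 6% to 8%.

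**4. Validity on average.** A simulation of 6,000 trials per setting applied a Shapiro-Wilk check and then the t-test or Mann-Whitney test. With no true effect and ρ = 0.5 or 0.7, the rejection rate was 5.1% and 5.5% for normal data, and 5.0% and 4.4% for lognormal data. The two-step rule does little harm to type I error.

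**5. Scale of the power difference.** For a true effect of 0.8 SD, which is an assumption and not a figure from the document, the two-step rule had 56% to 57% power on normal data and 52% to 53% on lognormal data. ANCOVA (log scale for the lognormal data) had 67% at ρ = 0.5 and 83% at ρ = 0.7.

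**The case against.** The strongest reply is that this concerns efficiency and is not an error. An unadjusted comparison of randomized arms is valid, and its standard error already allows for chance imbalance on average. The trial is a 30-patient pilot with a safety primary outcome and no efficacy power target, so power for an assumed effect is not its criterion. An unadjusted SD is still a usable, if anything conservative, input to phase 2. The size of the gain depends on a correlation that nobody has stated, and at 0.3 it is small. All of this stands, and it limits the weight of the point. It does not supply a reason to ignore a baseline value that is already collected.

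Four stronger readings might be inferred, and the document supports none of them.

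- **The tests are invalid.** They are not: average type I error stays near 5%.
- **Imbalance will be as large as any plausible effect.** The article gives no plausible clinical effect on NIHSS or volume, and severity is limited to 6 to 25.
- **The abstract contradicts the analysis.** It says that "the secondary outcomes include changes in functional outcome and infarction volume". This is loose wording: functional outcome there is most naturally mRS, and the analysis rule could be applied to a change score.
- **The missing time point is a defect.** An article may leave that to the full protocol or analysis plan.

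The condition for moving to phase 2 refers to adverse reactions and 90-day prognosis. It does not name NIHSS or infarct volume, so an effect on that decision cannot be claimed either.

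**Conclusion.** The point holds as a worthwhile improvement to secondary analyses. The article fixes unadjusted tests and the rule for choosing between them, so this is not a matter of detail left out. Over the assumed correlations, adjustment removes between 9% and 64% of the variance before the small-sample cost. The benefit is minor at 0.3 and substantial from 0.5 upward. One correlation has been applied to both outcomes and all visits for simplicity; the true values may differ. The imbalance figure rests on the assumed NIHSS SD. The loss is in precision and in accuracy given the imbalance that actually occurs.

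**What to change.** Replace the normality-driven choice of test with an analysis fixed in advance:

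- **Infarct volume:** ANCOVA of log(volume + 1) on treatment and baseline log(volume + 1).
- **NIHSS:** ANCOVA of follow-up NIHSS on treatment and baseline NIHSS. Alongside it, prespecify a rank-based ANCOVA with deaths given the worst rank, so that the conclusion does not rest on untransformed, possibly skewed scores or on survivors alone.
- **Reporting:** the adjusted difference with a 95% confidence interval for each outcome. The residual SD is also worth giving for phase-2 planning.

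The cost is about one degree of freedom per model and a change of wording, including a sentence on how deaths enter the analysis. No additional visits, scans or patients are needed.
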